## **4. STUDY OBJECTIVES**

### **4.1 Overall Objective**

The purpose of this project is to develop a new motivational intervention model for young adults admitted in the ER with alcohol intoxication and test the efficacy of this new model using a randomized controlled trial comparing it to a control condition receiving a minimal intervention (structured brief advice).

### **4.2 Primary Objective**

The study seeks primarily to determine the effect of a motivational intervention compared to a control condition receiving a minimal intervention (structured brief advice) to decrease alcohol use and alcohol-related problems among young adults admitted in the ER with alcohol intoxication.

### **4.3 Secondary Objectives**

Secondary objectives are to evaluate the mechanisms of the intervention effects by evaluating moderators of the effect (i.e. under which circumstances the effect is observed), mediators of the effect (i.e. how the effect is translated into actual behavior change), moderated mediation (i.e. if the effect is transmitted through the designated mediators only under specific circumstances), as well as by exploring intervention successes and failures using qualitative analyses.

### **4.4 Safety Objectives**

Not applicable.

## 5. STUDY OUTCOMES

### 5.1 Primary Outcome

Primary outcomes measures will be

a) the number of Heavy drinking days over the last month (HDD, i.e. the number of days with 6 standard drinks or more, equivalent to 60 grams of pure alcohol or more) measured using a 30-day Timeline Follow-back technique (TLFB; Sobell and Sobell, 1995), see Chapter 9.2.1 for assessment details, and

b) the Short Inventory of Problems (SIP) total score (Kiluk *et al.*, 2013),

both measured over 3 follow-up times (3-, 6-, and 12-month after intervention).

These two measures were chosen as they are validated and largely used measures of change in alcohol use and alcohol-related problems, which are behaviour changes targeted by our motivational intervention.

### 5.2 Secondary Outcomes

Secondary outcomes measures will be

a) Weekly drinking amount (i.e. number of drinks per week, derived from the TLFB).

b) Frequency of alcohol-related consequences (derived from 9 alcohol-related consequences adapted from Wechsler *et al.*, 1994). Consequences will be measured over the same 3 follow-up times (3-, 6-, and 12-month after intervention). Consequences are another validated way of measuring alcohol-related problems.

c) SIP sub-dimension scores (Physical, Social, Intra-personal, Inter-personal, and Impulse control; Kiluk *et al.*, 2013). These scores will be measured over the same 3 follow-up times (3-, 6-, and 12-month after intervention). Sub-dimensions of the SIP instrument have been proposed as additional variables of interest. Intervention might have an effect on different sub-dimensions but not other.

d) Proportion of patients with hazardous or harmful drinking status (Alcohol use disorder identification test - AUDIT score  $\geq 8$ ; Babor *et al.*, 2001) at 12-month follow-up. The AUDIT was developed by the WHO and is largely used to evaluate the effect of brief alcohol intervention. The reference period is 12 months and will thus be assessed only at this follow-up.

e) Proportion of patients who started alcohol treatment and of patients readmitted to the ER over the 12-month follow-up period. These will be measured at 3 follow-up times (3-, 6-, and 12-month after intervention). Effective referral to alcohol treatment and/or avoidance of alcohol-related ER readmission is a secondary objective of the tested intervention.

f) Proportion of patients who started alcohol treatment and of patients readmitted to the ER according to Lausanne University Hospital medical records. Participants will be asked for an additional, non-mandatory consent to have access to their administrative records at Lausanne University Hospital. This measure will be used as a confirmatory measure of patient self-report. It will also allow for evaluating participants lost to follow-up.

g) Heavy drinking according to Ethyl glucuronide (EtG) concentration in head hair. EtG has been presented as the only biomarker that can conclusively discriminate active heavy drinkers from social and non-drinkers (Crunelle *et al.*, 2014). In a study conducted at Lausanne University Hospital (Kharbouche *et al.*, 2012), cutoff values were determined to discriminate at-risk drinkers and heavy drinkers. Based on this study and others, cutoff values were proposed by the Society of Hair Testing (at-risk drinkers:  $>7$  pg/mg EtG in hair; heavy drinkers :  $>30$  pg/mg; Kintz, 2015). Participants in the present study will be asked for consent to take a 2-3 centimeters long strand of hair (diameter of pencil lead) for EtG testing at baseline, 6-, and 12-month follow-up. EtG testing will be a secondary, confirmatory outcome measure. Participants with head hair shorter than 2 centimeters or refusing hair sampling will not be excluded from the study. Research on cosmetic treatments of hair showed that permanent coloration, decoloration, and permanent wave might reduce EtG concentration (Kerekes and Yegles, 2013; Crunelle *et al.*, 2015). The occurrence of such treatments will be measured in the questionnaire and taken into account when interpreting EtG measures. Potential inconsistencies between this measure and other alcohol use measures will not lead in correction of alcohol use measures. Nonetheless, secondary analysis of the data to compare these different measures is planned and will be the focus of an article.

### 5.3 Other Outcomes of Interest

Additional measures for intervention mechanisms study will also be assessed at different time points (see table below) in order to conduct moderation and mediation analysis (see chapter 11.4.3 Secondary analysis).

|                                                                    | Baseline | Post-session | 1-month | 3-month | 6-month | 12-month |
|--------------------------------------------------------------------|----------|--------------|---------|---------|---------|----------|
| Alcohol use disorder severity (Babor et al. , 2001)         | x        |              |         |         |         |          |
| Readiness Rulers (Rollnick, 1998)                                  | x        | x            |         |         |         |          |
| Actual-ideal discrepancy (McNally et al. , 2005)            | x        | x            | x       | x       | x       |          |
| Alcohol-related expectancies (Ham et al. , 2005)            | x        |              | x       | x       | x       |          |
| Depression/Anxiety (Kroenke et al. , 2009)                  | x        |              |         |         |         |          |
| Attribution of injury to alcohol (Longabaugh et al. , 1995) | x        |              |         |         |         |          |
| Severity of ER admission and diagnosis (medical records)           | x        |              |         |         |         |          |
| Quality of life (de Boer et al. , 2004)                     | x        |              | x       | x       | x       |          |
| Patient rating of the treatment (Lee et al. , 2007)         |          | x            |         |         |         |          |
| Working alliance inventory (Horvath and Greenberg, 1989)           |          | x            |         |         |         |          |
| Trait reactance (Shen and Dillard, 2005)                           |          |              | x       |         |         |          |

### 5.4 Safety Outcomes

No specific safety outcomes will be measured. See Chapter 10. Safety.

## 6. STUDY DESIGN

### 6.1 General study design and justification of design

#### 6.1.1 Development and pre-test of a new intervention model (Aim 1)

This part corresponds to Aim 1 of the present project which consists of an iterative process aiming to develop and pre-test the intervention model through qualitative evaluation and refinement of the intervention tool. This process is planned over a 3-month period. The resulting intervention will be tested in the proposed randomized controlled trial (Aim 2).

As more thoroughly described above (see Chapter 3, Background), an initial intervention model was developed based on the existing literature on alcohol-related brief motivational interviewing (BMI) tailored to young adults as well as on the investigators' clinical and research experience. This first phase aims to pre-test the initial intervention model through iterative testing and refining by conducting one first round of experimental sessions with qualitative evaluations of the interventionists' and patients' experience (N=6), one round of international experts' consultation, and a second round of 6 experimental sessions with qualitative evaluations of the interventionists' and patients' experience.

#### 6.1.2 Randomized controlled trial (Aim 2)

##### 6.1.2.1 *Treatments / intervention*

The experimental treatment will be the brief motivational intervention (BMI) developed and pre-tested in the first phase of the project. BMI will be delivered while in the ER by a qualified research clinician (psychologist, clinical social worker, or nurse) and will last between 20 to 60 minutes. After the session, the interventionist sends a letter summing up the discussion (i.e., context, discussion, aims and encouragements) to the participant. Based on participant's agreement, booster session by phone will be conducted after **1 week 2-weeks**, 1 month, and 3 months.

**"2 weeks" changed to "1 week", 28.11.2016 (before inclusion of first participant)**

##### 6.1.2.2 *Population to be studied and the number of participants to be included*

All consecutive patients between the age of 18 and 35, admitted in the ER (for any cause) and having alcohol intoxication (>0.5 gram/liter BAC or clinical indication of alcohol intoxication) will be contacted by a member of the research staff (see figure below). Exclusion criterion will be a) life threatening conditions; b) detainees or medico-legal admissions; c) not being fluent in French; d) currently receiving another alcohol or substance use treatment; e) psychiatric or medical contraindications preventing patients understanding informed consent, fulfilling questionnaires, and participating in the intervention (evaluated using an adaptation of the University of California, San Diego Brief Assessment of Capacity to Consent; McCormack et al. 2014). Patients meeting inclusion criterion but being too intoxicated will be contacted by research staff once they have sobered up.

Targeted sample size is of 344 participants. This number was derived using a program for power analysis in longitudinal design (Rochon, 1998) which showed that a sample of N=172 patients per group (with attrition of 5-20% over follow-ups) will be required to detect small/medium effect sizes (.25), with power at .8, alpha at .05, and moderate autocorrelation dampening in GEE models for the primary outcomes. Primary analyses will use all data available from all participants included in the trial. Analysis will be performed in an intention to treat paradigm (i.e. participants having left the ER without finishing the intervention, and/or not receiving intervention booster sessions will be analyzed in the intervention group). In the event that we identify systematic mechanisms of missingness, we will explore varying techniques to impute missing data (Little and Rubin, 2002). (See also chapters 7.4 Criteria for withdrawal/discontinuation of participants, 11.4 Planned analyses, and 11.5 Handling of missing data and drop-outs).

##### 6.1.2.3 *Blinding*

Participants will be blinded to which kind of interventions they are receiving. Clinicians cannot be blinded to the type of intervention they will have to deliver. All data collection through the eCRF will be undifferentiated according to the allocated study group, thus non-indicative to investigators and

follow-up interviewers.

**6.1.2.4 Kind of comparator(s), (e.g. placebo, no treatment, active drug, dose-response, historical and study configuration (parallel, cross-over))**

BMI will be tested against a control comparison minimal intervention (Brief advice).

*Brief advice* will be delivered in approximately 5 to 10 minutes. It will be led by research clinicians and will consist of a standardized computer-based brief structured feedback and advice to cut down drinking, with referral to specialist services for the more severe patients (based on the Alcohol Use Disorders Identification Test score included in the baseline assessment).

**6.1.2.5 Method of assignment to treatment/intervention**

Simple randomisation (parallel, unstratified, 1:1 repartition ratio).

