## **6.2 Methods of minimising bias**

### **6.2.1 Randomisation**

Randomization will be performed using an algorithm implemented in the same software used to collect baseline assessment (secuTrial). The unit will be the participants and there will be no stratification. There will be the exact same chance for each participant to receive intervention a) or b).

The algorithm will be developed and implemented by the Lausanne Clinical Trial Unit and will thus be totally independent of the research field staff and research investigators.

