## **9.3 Procedures at each visit**

### **9.3.1 Day 1 – Inclusion, Baseline procedures, Intervention (in the ER)**

- A. Inclusion/Exclusion criteria from medical file/ER exam
  - Age
  - Blood alcohol concentration at admission (test made by ER staff)
  - Life threatening conditions
  - Detainees or medico-legal admissions
  - Medical or psychiatric contraindications preventing contact with patient
- B. Inclusion/Exclusion criteria assessed by research staff
  - Being fluent in French
  - Not currently receiving another alcohol or substance use treatment
- C. Consent process
  - Information sheet
  - No psychiatric or medical contra-indications preventing patients understanding informed consent, fulfilling questionnaires, and participating in the intervention (evaluated using an adaptation of the University of California, San Diego Brief Assessment of Capacity to Consent; McCormack et al. 2014)
  - Signing consent form
- D. Contact information
  - Name, Address, Phone
- E. Baseline questionnaire
  - Socio-demographic questions
  - Alcohol Use Disorder Identification Test
  - Substance use
  - Attribution of ER admission to alcohol
  - Readiness Rulers
  - Alcohol-related expectancies
  - Actual-ideal drinking discrepancy
  - Depression
  - Quality of Life
- F. Randomization
  - Software-based automatic allocation to study group (BMI vs BA)
- G. Intervention
- H. Post-session questionnaire
  - Patient rating of the treatment (paper/pencil questionnaire to be placed in a sealed envelope by the participant and later entered by research assistant to avoid that research

- clinicians have access to participant's rating of the session)
  - Readiness Rulers
  - Actual-ideal drinking discrepancy
- I. Counselor's rating of the treatment
  - Working alliance inventory
- J. Head hair sampling for Ethyl Glucuronide concentration analysis
  - Additional information and consent procedure
  - Sampling of 2-3 centimeters long strand of hair (diameter of pencil lead)
- K. Additional information on admission (medical records, not in presence of patient)
  - Admission and discharge time
  - Diagnosis
  - Use of restraints
  - Passage in resuscitation area
  - Orientation at ER discharge

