### **11.4 Planned Analyses**

#### **11.4.1 Datasets to be analysed, analysis populations**

Primary analyses of the efficacy of the intervention (randomized controlled trial) will use all data available from all participants included in the trial. Analysis will be performed in an intention to treat paradigm (i.e. participants having left the ER without finishing the intervention, and/or not receiving intervention booster sessions will be analyzed in the intervention group).

Secondary analysis of mechanisms (Aim 3 of the project) will use data available for the corresponding analyses (e.g. participants with audio-recorded sessions for psycholinguistic coding; randomly selected sub-sample for qualitative analyses). Also, moderation analyses are designed as part of the mechanism analyses. For these, the relative efficacy of the BMI will be tested as an interaction with participants' characteristics, such as age, gender, alcohol problems severity, readiness to change, or personality traits.

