#### 11.4.2 Primary Analysis

We will test intervention effects over time by comparing groups on the 2 primary and 6 secondary outcomes. For repeated measures, analyses will be conducted using generalized estimating equations (GEE) with robust standard error estimate (Liang and Zeger, 1986). This approach offers an extension of regression analysis to the case of correlated observations over time; it allows for specification of the assumed correlation structure as well as the appropriate link functions to handle dependent variables with a normal distribution, dichotomous outcomes, count data (Poisson), and over-dispersed count data (negative binomial). Models will all be adjusted for the baseline AUDIT score. For outcomes measured at 12-month only, analyses will be conducted using baseline adjusted regression models.

Analyses will be performed at the completion of data collection.

Analyses will be performed by the study PI ([name]), in collaboration with research collaborator [name], and consulting from study co-Is ([name], [name], [name]) and international collaborators ([name], [name]).

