#### 11.4.3 Secondary Analyses

Analyses of intervention mechanisms (Aim 3 of the project) will include the following analyses:

*Moderation.* Separate GEE models will test the main effect of treatment on outcome, followed by the effect of each moderator variable, and then the interaction of the treatment with each moderator variable.

*Mediation.* To examine mediators of the main effect of the MI intervention on outcomes, we will use Model 4 of the PROCESS algorithm developed by Hayes (2013). Here, regression analyses are used to test path *a* (the effect of the treatment condition on the hypothesized mediators) and path *b* (the effect of each respective mediator on outcomes, while also controlling for the treatment effect on outcomes). Then indirect effects are estimated using bootstrapping, a nonparametric resampling procedure that does not impose the assumption of normality of the sampling distribution (Hayes, 2013; Preacher & Hayes, 2008).

*Moderated mediation* aims at measuring if the effect is transmitted through the designated mediators only under specific circumstances. Several models of the PROCESS algorithm (e.g. 7, 9, 58) allow calculation of moderated mediation (also known as conditional indirect effects) (Hayes, 2013) (Hayes, 2013). These different models specify which path (*a*, *b*, both) of the mediated relationship are moderated. As in mediation, bootstrapping is used to derive conditional indirect effects.

*Qualitative analyses.* In addition to the quantitative analysis of interventions' mechanisms exposed above, we will use qualitative techniques to analyze intervention and follow-ups feedback. A random sub-sample of 20 BA and 20 MI sessions will be transcribed and analyzed using thematic analysis and recursive abstraction techniques (Maxwell, 2005). In addition, semi-structured interviews will be conducted after the 1-month and 12-month follow-up questionnaire with another randomly selected 10 patients having received BA and 10 MI sessions. Topics addressed will be qualitative assessment of potential short-/long-term changes experienced during the follow-up period and their relation or not with the intervention received.

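### Sex and age could be added to AUDIT as pre-specified covariates in the efficacy models: a cheap gain in precision, not the repair of an error

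*Protocol*

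**What the plan says.** Protocol section 6.1.2.5 gives the allocation as "Simple randomisation (parallel, unstratified, 1:1 repartition ratio"). Section 6.2.1 confirms it: "The unit will be the participants and there will be no stratification".

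For the analysis, section 11.4.2 states: "Models will all be adjusted for the baseline AUDIT score". It names no other covariate for the efficacy models; outcomes measured only at 12 months get baseline-adjusted regression.

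Age and gender enter elsewhere. Section 11.4.1 lists them among patient characteristics whose interaction with treatment will be tested, "such as age, gender, alcohol problems severity, readiness to change, or personality traits". Section 11.4.3 describes models that start from the treatment effect, "followed by the effect of each moderator variable, and then the interaction of the treatment with each moderator variable".

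The baseline procedures in section 9.3.1 list age under eligibility and include "Socio-demographic questions". Sex is not itemised there, but its collection follows safely from that entry and from the planned moderation by gender.

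Section 6.2.2 says that the data analysts are not blinded, and section 11.4.2 gives the analysis to the principal investigator with collaborators.

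**The concern.** Neither the allocation nor the stated efficacy model deals with sex or age. Two features of the protocol make this worth a second look.

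- **One threshold for everyone.** Heavy drinking days are defined for all participants as "the number of days with 6 standard drinks or more, equivalent to 60 grams of pure alcohol or more". It is plausible that sex predicts this count beyond what AUDIT captures. The protocol does not say so, and the argument does not carry over directly to the SIP score or to age.
- **Unblinded analysts.** If the arms turn out visibly different in sex or age, the decision to adjust would be taken by people who know the allocation. Naming the covariates in advance removes that discretion.

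At stake is a modest loss of precision and an avoidable choice after the data are seen. The validity of the test is not at stake.

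**Working it through.** **Inputs from the protocol (section 11.2).** 172 per arm (344 in total), standardised effect 0.25, power 0.80, alpha 0.05 (taken as two-sided), attrition 5–20%. The primary outcomes are analysed at three follow-up times (section 5.1).

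**Assumed inputs (not in the protocol).** Share of men p = 0.6–0.8; sex difference after AUDIT d = 0.2–0.5 SD. The count outcome is treated on an SD scale, which is an approximation.

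**1. The plan's own figure.** One time point needs 2 × (1.960 + 0.842)² / 0.25² ≈ 252 per arm. With three visits, retention of 95%, 87.5% and 80%, and an assumed correlation of 0.5 with damping from none to full, the GEE calculation gives 183 to 167 per arm. So 172 is plausible. It cannot be confirmed, because the correlation is not given as a number. This point does not dispute it.

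**2. Chance imbalance in sex.** SD of the difference in the share of men = √(2p(1−p)/172); 95% limit = 1.96 × SD.

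| p | SD (points) | 95% limit (points) |
|---|---|---|
| 0.6 | 5.3 | 10.4 |
| 0.7 | 4.9 | 9.7 |
| 0.8 | 4.3 | 8.5 |

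**3. Shift in one realised estimate.** Shift = limit × d.

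- Smallest: 0.0845 × 0.2 = 0.017 SD, or 7% of 0.25.
- Largest: 0.1035 × 0.5 = 0.052 SD, or 21% of 0.25.

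The standard error implied by 80% power is 0.25 / 2.80 = 0.089 SD, so these limits are about 0.2 and 0.6 of one standard error. That standard error already includes this source of variation.

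**4. Gain from adjusting for sex.** R² = p(1−p)d²; power = Φ(2.8016/√(1−R²) − 1.96).

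- Smallest: R² = 0.8 × 0.2 × 0.2² = 0.0064, power 80.3%.
- Largest: R² = 0.6 × 0.4 × 0.5² = 0.06, power 82.4%.

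This takes d in SDs of the outcome that enters the treatment comparison. If d is instead in single-visit SDs and the sex gap is the same at all visits, R² is (SD of imbalance × d)² / 0.0892². That gives 0.009 to 0.088 and power of 80.4% to 83.5%. The conclusion is the same.

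**5. Sex and age together.** Assumed partial R² of 0.01, 0.02, 0.05 and 0.10 gives power of 80.4%, 80.8%, 82.0% and 84.0%.

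**6. Validity.** A simulation of 20,000 trials with 344 patients, 70% men, a sex effect of 0.4 SD and an age effect of 0.15 SD per SD gave type I error of 0.052 with AUDIT only and 0.053 with sex and age added. Power was 0.798 and 0.826.

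**The case against.** The strongest reply is that nothing here is wrong. Section 11.4.2 says that all models adjust for AUDIT; it does not say that they adjust for nothing else. A statistical analysis plan, not available for this review, may add covariates. The protocol never calls sex or age prognostic. It gives them as examples in an open list of possible moderators, so choosing these two is partly a matter of judgement. The benefit is small and rests on assumed values. Simple allocation also suits this trial: the clinicians who recruit patients also deliver both interventions unblinded, and simple allocation cannot be predicted.

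Most of this stands. A reader might infer that unstratified allocation biases the comparison, or that the protocol rules out other covariates. The documents support neither. Randomisation protects the test whether or not the arms happen to balance, section 11.4.2 contains no word of exclusion, and the moderation models in section 11.4.3 already add each moderator as a main effect.

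The reply does not remove the suggestion. The protocol itself states the covariate adjustment for its efficacy models, so extending that statement is a comment on a choice it makes. The unblinded analysis gives a reason to settle the matter in advance.

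**Conclusion.** This is a cheap improvement. The design facts hold: allocation is unstratified, AUDIT is the only covariate named for the efficacy models, and age and gender are used only as moderators. The consequence is a small loss of precision and an open covariate choice for unblinded analysts.

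For sex alone the gain is about 0.3 to 2.4 power points. The upper end needs 60% men and a 0.5 SD sex difference after AUDIT, and neither figure is in the protocol. Age may add something, by an amount the protocol gives no means to estimate. The 7–21% figure is a 95% limit on movement within one trial. It should not be read as bias.

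**What to change.** In section 11.4.2, extend the adjustment sentence so that all primary and secondary efficacy models include the baseline AUDIT score, sex, and age as a continuous variable. Leave the randomisation in sections 6.1.2.5 and 6.2.1 as it is.

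The cost is one sentence. No new data are needed, given that sex is among the socio-demographic questions. In the log-link count models the treatment rate ratio keeps its meaning after adjustment. In logistic models for the binary secondary outcomes (hazardous drinking status, treatment start, readmission), the odds ratio becomes conditional on two more covariates, and the report should say so.
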